**Deployments**			
**1. Timing, frequency, duration, and nature.**	Calculated from deployment records using data from DoD Contingency Tracking System and Personnel Tempo files.	Records	
**2. Combat experiences.**	Combat Exposure Scale (α = .85) [60]	Interview	
**Mediating Processes**			
**1. Parents’ Mental Health.**			
***a. Psychological health*:**	Anxiety (GAD-7) (α = .92); [61]	Survey	
	Depression (PHQ-8) (α = .85); [62, 63]	Survey	
	Post-traumatic stress PCL-5 (α = .94); [64, 65]	Interview	
	Spirituality DURAL (α = .78 to .91) [66]	Interview	Interview
	General Life Satisfaction [59]	Survey	
	Meaning and purpose (α>.90) [59]	Survey	
***b. Alcohol use*:**	AUDIT (α = .80); [67, 68]	Survey	
***c. Post-traumatic growth*:**	Post-traumatic Growth Inventory Short Form (10; α = .89);[69]	Survey	
***d. Medical records*:**	MDR records psychiatric diagnoses since deployment: • Mood Disorders (296.0–296.9, • Anxiety Disorders (300.0–300.9), and • Psychoactive Substance Use; 303.0–305.8.	Records	

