Deployment history information will come from the Contingency Tracking (CTS) and Personnel Tempo (PERSTEMPO) files, and will include reasons for deployment (e.g., training, contingency operations), dates, locations, and hazardous duty pay status. Medical record data will include health care utilization and diagnoses from the Medical Data Repository (MDR) including mental health diagnoses of both parents since the first deployment of the service member(s); parents’ physical injuries resulting from operations of war and screening and diagnosis of Traumatic Brain Injury; and children’s lifetime outpatient and inpatient visits with documentation of childhood disorders (e.g., Autism) and psychiatric disorders (e.g., mood and anxiety disorders). Outcomes of interest will include multiple indicators of children’s social-emotional development, behavior, academic performance, and health. Analyses will focus on multilevel examinations of direct, mediated, and moderating relationships between early exposure to parental wartime deployment and later youth outcomes. The study has been approved by the Institutional Review Board at the Department of Defense Naval Health Research Center. Data collection began in the spring of 2023, and recruitment is expected to continue for 16 months.

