#### Analyses for aim 1: To assess direct relationships between the timing, frequency, duration and content of siblings’ early exposures to parental deployments and later youth adjustment

Maladjustment is hypothesized to be greater for children whose exposures began earlier (operationalized as child age at first deployment, including gestational age, coded from archival data), were more frequent (i.e., total number of deployments during the child’s lifetime) prolonged (i.e., total days deployed), ended more recently (i.e., days since end of most recent deployment), or who were exposed to deployments where parents’ experiences were more traumatic (i.e., total scores on self-report Combat Exposure items). These hypotheses will be tested using a SEM framework, where a series of path models will estimate the direct effects of deployment characteristics on each indicator of adjustment. Paths from the independent variables will be tested concurrently, thus establishing the unique association for each deployment risk factor. Interactions between different deployment components—frequency, duration, timing, and content—will also be examined to determine whether long-term effects of deployment are exacerbated or mitigated for various deployment combinations. Within-family comparisons will be conducted to determine whether these direct effects differ across siblings.

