#### Analyses for aim 2: To assess the role of parents’ psychological health and family processes in mediating relationships between siblings’ early exposures to parental deployment and later youth adjustment

This aim highlights four indirect pathways through which deployment(s) influence youth adjustment. Deployment factors studied in Aim 1 are expected to be negatively related to parents’ psychological health, parental efficacy, marital relationship quality, and family functioning at Time 1, which in turn will be positively related with youth adjustment at Time 2. The magnitude and statistical significance of the indirect effects of deployment through each of these processes will be tested using the INDIRECT command within Mplus, which employs a product of coefficients method of testing mediation [121] and the bootstrap method to compute standard errors for the significance test [122]. Importantly, the four indirect pathways will be tested concurrently, highlighting not only which pathways are critical for understanding the potential enduring effects of parental deployments on youth adjustment, but also the relationships among them. Differences across siblings also will be assessed.

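### The record-based parental mental-health item counts diagnoses over a period whose length depends on the deployment dates, so part of Aim 2's psychological-health pathway can appear with no true effect

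*Protocol article*

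**What the plan says.** Table 2 (Mediating Processes, 1. Parents' Mental Health, item d) gives the record-based item as "MDR records psychiatric diagnoses since deployment", covering mood, anxiety and substance-use codes. The Overview of study design says where the count begins ("mental health diagnoses of both parents since the first deployment of the service member(s"). Neither place gives it a fixed length.

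Analyses for aim 1 define timing as "child age at first deployment, including gestational age, coded from archival data", frequency as "total number of deployments during the child’s lifetime", duration as total days deployed, and recency as "days since end of most recent deployment". These paths are estimated concurrently. Analyses for aim 2 then use the same factors as predictors of the mediators: "Deployment factors studied in Aim 1 are expected to be negatively related to parents’ psychological health", with the mediators placed at Time 1.

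The covariates in Model building and estimation are parental demographics and employment, family type and size, branch and paygrade. Child age and observed time are not among them. Analyses of aims mentions Poisson and binomial capability but no offset. Data cleaning promises timing variables built from child age and deployment dates, but does not connect them to the diagnosis count.

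**The concern.** A parent first deployed around the child's birth has been observed for many more years than one first deployed when the child was nearly 6. Cumulative diagnoses rise with years observed, so the first parent will tend to have more of them whether or not deployment affects mental health. The result would be a deployment-to-mediator path created by the measurement and carried into the indirect effect. Where it falls on age at first deployment, its sign agrees with the hypothesis (earlier exposure, worse parental health), so it would read as confirmation. Bootstrap standard errors do not remove a built-in association.

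**Working it through.** **1. Window length.** Let A be the child's current age and a the child's age at first deployment. When that is also the parent's first deployment, observed time is T = A − a. With ages 11 to 16 and qualifying exposure from gestation to age 6 (Sample; Analyses for aim 1):
- shortest: 11 − 6 = 5 years
- longest: 16 + 0.75 = 16.75 years
- ratio: 16.75 / 5 = 3.35

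T also equals total days deployed, plus gaps between deployments, plus time since the last one ended. If the parent deployed before the child's life, T is longer by that interval.

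**2. Effect on an ever/never flag.** With constant yearly rate r (assumed), P(any diagnosis) = 1 − exp(−rT). For a 14-year-old, first deployment at birth gives T = 14 and at age 5.9 gives T = 8.1:

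| r per year | T = 14 | T = 8.1 |
|---|---|---|
| 0.01 | 13% | 8% |
| 0.03 | 34% | 22% |
| 0.05 | 50% | 33% |

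**3. Yardstick.** The plan gives no figure for this item, so Table 1 serves for scale. Its family-level detectable beta is (1.960 + 0.842) / √1095 = 0.085 cross-sectionally and 2.802 / √1917 = 0.064 for repeated measures. Both reproduce.

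**4. Age at first deployment alone.** Null simulations used 712 families, unweighted, with an ever/never flag, a uniform from −0.75 to 6, full record capture and no deployment effect. At rates of 1 / 3 / 5% per year:
- spurious standardized beta: −0.06 / −0.09 / −0.11
- false rejection at nominal 5%: 29-33% / 67-78% / 84-86% across runs

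**5. Four deployment factors entered together.** The result depends on the spacing of later deployments, which the protocol does not give:

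| Spacing (assumed) | Age at first deployment | Days since last |
|---|---|---|
| Clustered soon after the first | about 0 | +0.09 / +0.15 / +0.18 |
| Spread over the window, 0.15 per year | −0.05 / −0.08 / −0.10, rejected 25 / 50 / 70% | small |

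Under either spacing, at least one of the four factors is falsely significant in 31-35% / 62-66% / 76-84% of data sets. Four independent tests would give 1 − 0.95⁴ = 19%.

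**6. What weakens it.** A wider set of concurrent-model runs used rates of 2-20% per year, between-family variation in rate, and spread deployments. False rejection for age at first deployment was:
- ever/never flag alone: 29-54%
- count alone: 35-88%
- flag as one of five equally weighted indicators: 7-12%

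The correlation of T with a is −0.80. It falls to −0.62 if half the families had a deployment 1-6 years before the first one in the child's life. In a separate run with age at first deployment alone, the spurious beta fell from about −0.095 to −0.053 when half the records ended 1-12 years after deployment, and to about −0.08 when half the parents first deployed before the child's life.

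**7. Does equal observation time cure it?** In the runs of step 6, a fixed 5-year window gave 4-7% rejection for age at first deployment. A Poisson model with log observed years as offset gave 3-7%. Both coefficients were about 0.

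**The case against.** Table 2 and the Overview list data to be obtained; they do not say that diagnoses will be scored as a lifetime flag or count, and such scoring is often left to a fuller plan. That stands as a limit: the size of the artefact is conditional on cumulative scoring. It does not remove the point, because the document does state the window, and the stated window varies with the exposure.

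The protocol also intends to code experiences by child age and relative to deployment. That shows dated coding is possible, but it commits to no fixed window, rate or control for observed time.

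A reader might infer that all of Aim 2, or the whole psychological-health pathway, is produced by this artefact. The documents do not support that. GAD-7, PHQ-8, PCL-5 and AUDIT come from surveys or interviews and have no such window. Latent variables are the stated default, and the item is one of several indicators. A reader might also infer that the concurrent model necessarily shifts the artefact to days since the last deployment. It does so only if later deployments cluster early, and there its sign opposes the stated hypothesis.

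Full record capture to the interview is also an assumption. The study includes families who have left service, and the protocol does not say how long their records continue.

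**Conclusion.** The concern holds in a limited form. The stated window for item 1d is tied to the Aim 1 exposures, and nothing stated in the protocol breaks that tie. Used on its own as a cumulative flag, with a 1-5% constant yearly rate and full capture, it produces false significance for age at first deployment taken alone in roughly 30-85% of data sets, with betas near or above the study's own detectable effects. As one of five equal indicators the figure is about 7-12%. Earlier parental deployments or truncated records reduce it further. Which coefficient carries the artefact in the concurrent model cannot be settled from the documents. Diagnosis rates, deployment spacing, scoring and record coverage are all assumptions here. Only the record-based part of the psychological-health pathway is at risk.

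**What to change.** In Table 2 item 1d and the Overview of study design, define the item over a window of equal length for every family, for example the 5 years from the start of the first shared deployment. Every eligible family has this much time, because at least one child was under 6 at the shared deployment and is now at least 11 (11 − 6 = 5).

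Alternatively, model diagnoses as a rate with the log of MDR-covered years as an offset. This also handles records that end early, but it assumes that the yearly rate is stable over follow-up. In either case, do not load a raw cumulative count or ever/never flag on the Time 1 psychological-health factor.

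A window counted back from the Wave 1 interview would also equalise time. It would, however, leave out much of the during- and post-deployment period that the section Model for the proposed study describes, so it fits less well.

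The cost is one sentence in the variable definition and a date filter or offset when the records are merged. No new data are needed. The downside is that fewer diagnoses are counted in the shorter window.

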**2. Parents’ Relationship.**			
***a. Quality of Marriage*:**	Quality of Marriage Index α = .88); [70, 71]	Survey	
***b. Problem Solving*:**	Perceptions of Collaboration (α = .80); [72]	Survey	
	Ineffective Arguing Inventory (α = .86 to .89); [73]	Survey	
***c. Conflict*:**	Conflict Tactics-2 Psychological Aggression (α = .79) [74]	Survey	
**3. Parenting Efficacy.**			
***a. Quality*:**	Parental Acceptance, Rejection, & Control (α = .89-.95); [75, 76]	Survey	Interview
***b. Coparenting*:**	Coparenting Questionnaire (α = .69 to.87) [77]	Survey	
***c. Differential treatment*:**	Perceptions of parental differential treatment (α = .89-.93) [78]		Survey
***d. Monitoring***	Perceptions of monitoring (α = .70 to .77) [79]		Survey
**4. Family Functioning.**			
***a. Overall*:**	Family Assessment Device (General Functioning) (α = .92); [80]	Survey	Survey
***b. Parent child relationship*:**	Items from the National Survey of Children’s Health [81]	Survey	
***c. Sibling relationship*:**	Network of Relationships Inventory (24; α>.70) [82]		Survey
**Moderating Relationships**			
**1. Parents’ Vulnerability Prior to Deployment.**			
***a. Life History***	Family members arriving or leaving; moving; changing schools, Parents: Adverse Childhood Experiences (ACES)	Interview	Interview
***b. Adverse Childhood Experiences***	Parents: Adverse Childhood Experiences (ACES)	Interview	
***c. Family of Origin Functioning***	Subscale of Deployment Risk & Resilience Inventory (α = .85); [83]	Interview	
***d. Psychological symptoms or substance use*:**	*MDR* records for psychiatric diagnoses including Mood Disorders (296.0–296.9, Anxiety Disorders (300.0–300.9), Psychoactive substance; 303.0–305.8;	Records	
**2. Children’s Vulnerability.**			
***a. Adverse experiences*:**	Adverse Childhood Experiences (Child); [81, 84]	Interview	
**3. Social Support.**			
***a. Informal support*:**	Emotional support (α = .91 - .97); [59, 85]	Interview	Interview
	Friendship (α = .91 - .97); [59, 85]	Interview	
***b. Formal support utilization*:**	Access and use of DoD/VA or community services [86]	Interview	
**4. Parental Wounds or Injuries related to Deplyment.**	*MDR records* for *physical injury* E990-E999, Injuries resulting from operations of war, and screening and diagnosis of Traumatic Brain Injury (V15.52l; V80.01).	Records	
**Adolescents’ Outcomes**			
**1. Social-emotional development.**			
***a. Competence*:**	Harter Self-Perception Profile for Children (36; α = .73 - .86); [87]		Interview
***b. Anxiety & Depression*:**	SCARED (α = .74 - .93); [88]		Survey
	Child Depression Inventory– 2 (α = .82); [89]		Survey
***c. Peer relationships*:**	PROMIS peer relationships (α = .92); [90]		Survey
***d. Attachment***	Adolescent Attachment Questionnaire (α = .62 to .80) [91]		Survey
***e. Post Traumatic Growth*:**	PTG Inventory for Children–R (α = .77 - .81); [92]		Interview
***f. Future Expectations*:**	Future Expectations (α = .70) [93]		Interview
***g. Positive Development***	Positive Youth Development (α = .80-.92) [94, 95]		Interview
**2. Behavior.**			
***a. Positive behavior*:**	Flourishing (α = .61);	Survey	
***b. Prosocial & problem behaviors*:**	Strengths and Difficulties Questionnaire (α = .76); [96]	Survey	Survey
***c. Risky behavior***:	Youth Risk Behavior Survey (mean kappa = 60.7%); [97]		Interview
***d. Substance use*:**	National Survey of Drug Use and Health [98] Youth Risk Behavioral Survey 2019 [97]		Survey
***e. Coping*:**	Seeking social support for emotional reasons subscale of the COPE scale (α = .85) [99]		Interview
**3. Academic performance**.	Academic engagement		Interview
	Problems at school [81]	Interview	
**4. Child Health Care Utilization.**	***MDR records*** for lifetime of visits (outpatient and inpatient) with documentation of diagnostic codes (312.0–316.0) with attention to disorders first diagnosed during childhood such as Attention Deficit Hyperactivity Disorder, Learning Disability/Developmental Delay, & Autism and codes (290–319) for commonly diagnosed psychiatric disorders in childhood including (Mood (296.0–296.9 and Anxiety Disorders (300.0–300.9).		Records

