## Abstract

Multiple adjustment difficulties have been associated with children’s exposure to recent parental wartime military deployments, but long-term consequences have not yet been systematically studied. This investigation will assess direct and indirect relationships between exposures to parental deployments early in life and later youth adjustment. Parents’ psychological health and family processes will be examined as mediators, and parents’ and children’s vulnerability and support will be examined as moderators. Archival data will be combined with new data gathered from two children and up to two parents in families where children will be aged 11 to 16 at the first data collection and will have experienced at least one parental deployment, for at least one child prior to age 6. Data are being gathered via telephone interviews and web-based surveys conducted twice one year apart. Outcomes are indicators of children’s social-emotional development, behavior, and academic performance. Notable features of this study include oversampling of female service members, inclusion of siblings, and inclusion of families of both veterans and currently serving members. This study has potentially important implications for schools, community organizations and health care providers serving current and future cohorts of military and veteran families.

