### Aim 1: To assess direct relationships between the timing, frequency, duration and nature of siblings’ early exposures to parental deployments and later youth adjustment

Youth whose deployment exposures began earlier in childhood, were more frequent or prolonged, and/or involved more traumatic [40] parental experiences are hypothesized to display less positive adjustment, and youth exposed to deployments with fewer such characteristics will display more positive adjustment. We will examine how these direct relationships differ between siblings, providing more sensitive tests than previously possible of the degree to which youth outcomes are a function of deployment, family, and child factors.

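### The child health-care outcome is set as lifetime visits with no start tied to deployment, so it mixes care before and after exposure in a share that depends on age at first deployment

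*Protocol article*

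**What the plan says.** The Overview of study design says the child medical data will cover "children’s lifetime outpatient and inpatient visits with documentation of childhood disorders" and then names health among the outcomes: "Outcomes of interest will include multiple indicators of children’s social-emotional development, behavior, academic performance, and health". Table 2 repeats the window in the Child Health Care Utilization row under Adolescents' Outcomes: "lifetime of visits (outpatient and inpatient) with documentation of diagnostic codes". Neither place gives a start date related to deployment.

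The same table does set windows for parents. The mediator row reads "MDR records psychiatric diagnoses since deployment", and a separate moderator row covers parents' psychiatric diagnoses under vulnerability before deployment.

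Aim 1 concerns the relation between "early exposures to parental deployments and later youth adjustment". Its analysis section takes the child's age at first deployment, gestation included, as the timing predictor. Model building and estimation lists controls for parents, family, branch and paygrade; child age is not among them.

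On the source, the Overview says medical records come from the DoD, while the Abstract stresses "inclusion of families of both veterans and currently serving members" and the Sample section includes the reserve component. The Innovation section nevertheless describes the archive as supplying visit and diagnosis information on everyone in the study.

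**The concern.** An outcome meant to show adjustment after an exposure should not count events from before it. For a child first exposed at age 4, a lifetime count credits four years of earlier care to the outcome side of the model. If the contamination were unrelated to exposure it would mostly dilute effects. Here it is tied to the exposure: the later the first deployment, the larger the pre-exposure part of the window. A timing effect can then appear, or be hidden, because of how the variable is built.

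Two further features matter. Older children have longer windows. And the sibling comparison, which the article presents as a main strength, is directly affected, because siblings share a deployment but differ in age when it happened.

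**Working it through.** The article states no figure that depends on this outcome, so there is nothing to reproduce. The arithmetic below uses the article's ages; rates and rate ratios are assumptions.

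**Inputs**
- Current age T: 11 to 16 (Sample).
- Age at first exposure a: from prenatal (a = 0) to just under 6 for at least one child (Sample), taken as 5.99 at the upper end. The other sibling may have been older.
- Visit rate constant with age, and a post-exposure rate ratio RR that does not depend on timing (assumptions).

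**1. Pre-exposure share of the lifetime window = a/T**

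| a | T = 11 | T = 13 | T = 16 |
|---|---|---|---|
| 0 | 0% | 0% | 0% |
| 3 | 27.3% | 23.1% | 18.8% |
| 5.99 | 54.5% | 46.1% | 37.4% |

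These are shares of time. They equal shares of visits only if the visit rate is constant.

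**2. Window length.** 16/11 = 1.45, so a 16-year-old has 45% more time to accumulate visits than an 11-year-old.

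**3. Effect on the timing predictor at a fixed current age.** Lifetime count relative to no effect = (a + RR × (T − a))/T. With RR = 1.5:
- a = 0: 1.50 at every T.
- a = 5.99, T = 11: (5.99 + 1.5 × 5.01)/11 = 1.23.
- a = 5.99, T = 13: 1.27.
- a = 5.99, T = 16: 1.31.

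With RR = 1.2 the fall is from 1.20 to between 1.09 and 1.13; with RR = 2.0, from 2.00 to between 1.46 and 1.63. No true timing effect was put in, yet earlier exposure looks worse, which is the Aim 1 hypothesis.

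**4. Siblings who share the same first deployment.** Time since exposure is the same for both, so the older sibling's extra window is entirely pre-exposure. Take siblings now 11 and 16, the younger exposed at 5.99:
- Younger: post-exposure 11 − 5.99 = 5.01 years.
- Older: age at exposure 5.99 + 5 = 10.99; post-exposure 16 − 10.99 = 5.01 years; pre-exposure share 10.99/16 = 69%.
- Raw lifetime count at RR = 1.5, in units of one year at the base rate: younger 5.99 + 7.515 = 13.505; older 10.99 + 7.515 = 18.505; ratio 1.37.
- Per year of life: younger 13.505/11 = 1.23; older 18.505/16 = 1.16.

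The raw count makes the later-exposed sibling look worse and the per-year count makes the earlier-exposed sibling look worse. Both differences are artefacts, and their direction depends on scaling.

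**5. After the change.** Counting only after first exposure and dividing by observed time gives RR × (T − a)/(T − a) = 1.50 at every age of exposure and for both siblings.

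**The case against.** The strongest reply is that Table 2 describes the data to be obtained, not the variable to be analysed. A lifetime extract is reasonable, and the remedy needs it for the pre-exposure baseline. A condensed article may leave the derivation rule to a fuller document. The article also plans timing variables indexed by child age and deployment dates (Data cleaning and preliminary analyses) and the coding of experiences relative to deployment (Model for the proposed study).

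Part of this stands: the extract is not the error, and it should be kept. But the row sits under Adolescents' Outcomes, and the same table gives parents' records explicit windows. Neither timing statement is applied to the visit outcome. They show that the change is feasible, not that it has been made.

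Two stronger readings are tempting and not supported.
- A reader might infer that years outside DoD records will be scored as no care. The article does not say so. It is silent on how such time is handled, and nothing in it allows the size of a gap to be worked out.
- A reader might infer that the outcome cannot measure later adjustment at all. That goes too far. Children exposed prenatally have no care before exposure, a post-exposure window can be derived if visits are dated, and this is one row in a long list of outcomes. The survey and interview outcomes are unaffected.

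**Conclusion.** The concern holds for this one outcome. As written, it combines care before and after exposure, with a pre-exposure share from 0% (prenatal) to about 37% at age 16 and 55% at age 11 for first exposure just before age 6. In an older sibling sharing that first deployment it could reach about 69%. The share depends on a tested predictor, and window length varies by up to 1.45 with an unlisted covariate. Under a constant visit rate and a true post-exposure rate ratio of 1.5, the apparent ratio falls to between 1.23 and 1.31 for exposure near age 6. The ratios are illustrations; the shares of time follow from the article's ages.

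On coverage, the conclusion is narrower. With DoD-only records and veteran and reserve families in the sample, the statement in the Innovation section about complete information is not backed by anything in the article and should be qualified. Neither the presence nor the size of under-recording is established.

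**What to change.** Keep the lifetime extract and change the derived variable.
- Define the outcome as visits and new diagnoses after the child's first exposure, or over a common age window that starts after first exposure for the children included.
- Model it as a rate with log observed time as offset. Analyses of aims names Poisson models as something the framework can handle, but does not assign one to this outcome, so the assignment should be stated.
- Adjust for child age, and use pre-exposure visits as a baseline covariate where they exist. Children exposed prenatally have none. Within sibling pairs sharing a first deployment, the difference in current age equals the difference in age at first exposure, so the age adjustment must draw on differences between families or on the common age window.
- Treat time without DoD record coverage as unobserved where coverage dates can be obtained, and qualify the Innovation statement.
- Reconcile the Overview and Table 2 wording with the windows used for parents.

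The cost is mostly derivation rules on dated records and deployment dates. Some children will contribute less record time. Monthly health-care eligibility is not among the DEERS fields the article describes, so coverage dates may have to be added to the data request.
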